## Primary and secondary objectives and outcomes: summary

|                    | Objectives                                                                                                                                                                  | Outcomes                                                                                                                                                                                                                                                                                                                                                                                                                                                                                                                                                                                                                                                                                                                                                                                         |
|--------------------|-----------------------------------------------------------------------------------------------------------------------------------------------------------------------------|--------------------------------------------------------------------------------------------------------------------------------------------------------------------------------------------------------------------------------------------------------------------------------------------------------------------------------------------------------------------------------------------------------------------------------------------------------------------------------------------------------------------------------------------------------------------------------------------------------------------------------------------------------------------------------------------------------------------------------------------------------------------------------------------------|
| Primary     | to assess the effectiveness of EarlyCDT-Lung test in reducing the incidence of patients with late-stage lung cancer at diagnosis, compared with standard clinical practice; | difference at 24 months after randomisation, between the number of patients with stage 3, 4 or unclassified lung cancer at diagnosis in the intervention arm, and those in the control arm;                                                                                                                                                                                                                                                                                                                                                                                                                                                                                                                                                                                                      |
| Secondary 1 | to assess the effectiveness of EarlyCDT-Lung test in improving the diagnosis of early-stage lung cancers;                                                                   | numbers, at 24 months after randomisation, in the different stages at diagnosis (3/ 4/ U/ other) in the intervention arm and the control arm;                                                                                                                                                                                                                                                                                                                                                                                                                                                                                                                                                                                                                                                    |
| 2           | to undertake a cost-effectiveness analysis of EarlyCDT-Lung test as a primary screening method in comparison to standard clinical practice;                                 | difference, after 2 years, in the costs and outcomes between the intervention arm and the control arm; cost-effectiveness of the intervention compared to standard clinical practice                                                                                                                                                                                                                                                                                                                                                                                                                                                                                                                                                                                                             |
| 3a          | to compare lung-cancer mortality, all-cause mortality and cancer-specific mortality in high-risk groups provided with EarlyCDT-Lung test, compared with standard practice;  | estimates, after 2 years, of lung cancer mortality, all-cause mortality and cancer-specific mortality in the intervention arm and in the control arm; assessment of significance of differences;                                                                                                                                                                                                                                                                                                                                                                                                                                                                                                                                                                                                 |
| 3b          | to compare long-term future mortality in high-risk groups provided with EarlyCDT-Lung test, compared with standard practice;                                                | estimates, after 5 and 10 years of long-term future mortality in the intervention arm and in the control arm; assessment of significance of differences;                                                                                                                                                                                                                                                                                                                                                                                                                                                                                                                                                                                                                                         |
| 4           | to obtain refined estimates of the sensitivity, specificity, positive predictive value and negative predictive value of EarlyCDT-Lung test;                                 | estimates, after 2 years of (i) the number of patients with stage 3, 4 or unclassified lung cancer at diagnosis in the EarlyCDT-Lung test-positive group and those in the EarlyCDT-Lung test-negative group and (ii) stage at diagnosis in the EarlyCDT-Lung test-positive and EarlyCDT-Lung test-negative group;                                                                                                                                                                                                                                                                                                                                                                                                                                                                  |
| 5           | to assess behavioural outcomes including smoking, psychological outcomes including cancer worry, anxiety, depression, distress specific to clinical investigations;         | scores at baseline, and follow-up on EQ5D, Hospital Anxiety and Depression Scale (HADS), Positive and Negative Affect Schedule (PANAS), Revised Illness Perception Questionnaire – Lung Cancer (IPQ-LC), Lung cancer risk perception, Health anxiety subscale of Health Orientation Scale (HOS) and the Lung Cancer Worry Scale (LCWS), Medication, smoking behaviour, demographic details. Follow-up questionnaires include same items, plus Impact of Events Scale (intervention group only), healthcare utilisation and dates and results of follow-up investigations for lung cancer (test positive group only). The HADS is not included in follow-up questionnaires. Follow-up questionnaires are administered between 1 and 24 months to subsets of the control arm and intervention arm; |

|          |                                                                                                                                                                                  |                                                                                                                                                                                                                                                                                                                                                           |
|----------|----------------------------------------------------------------------------------------------------------------------------------------------------------------------------------|-----------------------------------------------------------------------------------------------------------------------------------------------------------------------------------------------------------------------------------------------------------------------------------------------------------------------------------------------------------|
|          |                                                                                                                                                                                  | (all participants in the EarlyCDT-positive group will be approached with the recruitment aim of 300 from this group collected at 1,3,6,12,18 and 24 months. The EarlyCDT-negative and control groups will be recruited at the same rate as the EarlyCDT-positive group with the recruitment aim of 300 from each group collected at 1,3,6 and 12 months). |
| 6 | to assess the effectiveness of EarlyCDT-Lung test on other clinical outcomes such as CVD, COPD, other cancers, hospital stays and outcomes identified through SMR linkage, etc.; | Incidence of other clinical outcomes such as CVD, COPD, other cancers, hospital stays, identified through SMR linkage, measured at 24 months, 5 and 10 years in the intervention arm and in the control arm; assessment of significance of differences;                                                                                                   |
| 7 | to assess uptake of subsequent investigations such as CXR, CT, bronchoscopy, etc.                                                                                                | numbers in all groups (EarlyCDT-Lung test-positive, EarlyCDT-Lung test-negative, control) undertaking subsequent investigations such as CXR, CT, bronchoscopy, etc.                                                                                                                                                                                       |

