a wide range of solid tumours, including lung cancer. The serum proteome provides an attractive source of potential biomarkers and because serum collection is minimally invasive it can be repeatedly surveyed for cancer biomarkers. AABs have been detected months to years before clinical diagnosis of breast and lung cancers, supporting the hypothesis that AABs could be incorporated into an early detection assay. Subsequent research studies have confirmed AABs to TAAs in patients with early stage lung cancer. AABs have been reported in lung cancer subjects up to 5 years before clinical diagnosis even where annual screening spiral CTs were being performed.

A serum assay has been developed and validated called Early Cancer Detection Test-Lung (EarlyCDT-Lung) that can detect 40% of lung cancers with a specificity of 90% by measuring autoantibodies to a panel of cancer antigens (p53, NY-ESO-1, CAGE, GBU4-5, Annexin1, & SOX2). Further confirmation of this sensitivity and specificity of the test for lung cancer using four new, independent sample sets has recently been published. A study of patient demographics showed no difference in autoantibodies based on age, gender and ethnicity. This autoantibody technology is different from CT scanning which in a prevalence screening test has a sensitivity of 67% for lung cancers developing over the following 12 months but with a low specificity of only around 49%. Indeed a prevalence CT screen will detect approximately 36% of the lung cancers which will develop in the next three years. If the EarlyCDT-Lung test has a three year 'look forward', as clinical data suggests, then the test will detect 40% of lung cancers which develop over this three year time period but with seven times fewer false positives than CT scanning. Two new autoantibodies (AABs) have recently been added to the panel (and one removed) and the test now measures seven; p53, NY-ESO-1, CAGE, GBU4-5, HuD, MAGE A4 & SOX2 and identifies 41% of lung cancers with an increased specificity of 93% (Chapman et al; 2012). The 7-AABs panel will be utilised in this study and all

statistical calculations are based on the 41% sensitivity and 93% specificity of the Early CDT-Lung test.

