### **1.4.2 Secondary Objectives**

1) to assess the effectiveness of EarlyCDT-Lung test in improving the diagnosis of early-stage lung cancers;

2) to undertake a cost-effectiveness analysis of EarlyCDT-Lung test as a primary screening method compared to standard clinical practice;

3a) to compare lung-cancer mortality, all-cause mortality and cancer-specific mortality in high-risk groups provided with EarlyCDT-Lung test, compared with standard practice;

3b) to compare long-term future mortality in high-risk groups provided with EarlyCDT-Lung test, compared with standard practice;

- 4) to obtain refined estimates of the sensitivity, specificity, positive predictive value and negative predictive value of EarlyCDT-Lung test;
- 5) to assess behavioural outcomes including smoking, psychological outcomes including cancer worry, anxiety, depression, distress specific to clinical investigations;
- 6) to assess the effectiveness of EarlyCDT-Lung test on other clinical outcomes;
- 7) to assess uptake of subsequent investigations.

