### **1.5.2 Secondary Outcomes**

- 1) numbers, at 24 months after randomisation, in the different stages at diagnosis (3/ 4/ U/ other) in the intervention arm and the control arm;
- 2) difference, after 2 years, between costs and outcomes in the intervention arm and in the control arm, cost-effectiveness of EarlyCDT-Lung test compared to normal clinical practice;
- 3a) estimates, after 2 years, of lung cancer mortality, all-cause mortality and cancer-specific mortality rates in the intervention arm and in the control arm; assessment of significance of differences;
- 3b) estimates, after 5 years and 10 years of long-term future mortality rates in the intervention arm and in the control arm; assessment of significance of differences;
- 4) estimates, after 2 years of (i) the number of patients with stage 3, 4 or unclassified lung cancer at diagnosis in the EarlyCDT-Lung test-positive group and those in the

EarlyCDT-Lung test-negative group and (ii) stage at diagnosis in the EarlyCDT-Lung test-positive and EarlyCDT-Lung test-negative group;

5) scores at baseline, and follow-up on in a survey administered prior to treatment allocation, including EQ5D, , Positive and Negative Affect Schedule (PANAS), Revised Illness Perception Questionnaire – Lung Cancer (IPQ-LC), Lung cancer risk perception, Health anxiety subscale of Health Orientation Scale (HOS) and the Lung Cancer Worry Scale (LCWS), Medication, smoking behaviour, demographic details. Follow-up questionnaires include same items, plus Impact of Events Scale (intervention group only), healthcare utilisation and dates and results of follow-up investigations for lung cancer (test positive group only). The HADS is not included in follow-up questionnaires. Follow-up questionnaires are EQ-5D, cancer worry, positive and negative mood, smoking behaviour including cessation intentions and attempts; scores in additional questionnaires administered at between 1 and 24 months to subsets of the control arm and intervention arm; (all participants in the EarlyCDT-positive group will be approached with the recruitment aim of 300 from this group collected at 1,3,6,12,18 and 24 months. The EarlyCDT-negative and control groups will be recruited at the same rate as the EarlyCDT-positive group with the recruitment aim of 300 from each group collected at 1,3,6 and 12 months).

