written to, explaining the test results and will be offered a follow-up visit or a telephone call if they wish. They will be advised of symptoms to watch for including persistent cough, coughing up blood, shortness of breath, weight loss or loss of appetite. They will be counselled to carry on having tests for other types of cancer if they are offered (e.g. bowel cancer test, mammograms, cervical smears).

Those in the control arm will be written to and thanked for their contribution to the study and advised and counselled identically to those with a negative test result.

All participants who agreed to donate blood for future will be advised that it will be used in cancer related research.

A patient specific section of the study website ([www.eclsstudy.org](http://www.eclsstudy.org)) containing Participant Information Sheets and research staff contact details will be available for participants to view.

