## **7.2 PROPOSED ANALYSES**

Characteristics of participants will be compared informally between treatment arms at baseline. The main analysis of the primary outcome will be intention-to-treat. Cox proportional hazards models will be used to estimate the hazard ratio of the rate of late stage lung cancer in the intervention arm compared to the control arm.

Participants who are lost to follow up will be censored. The models will adjust for age, gender smoking history and practice. If appropriate, random cluster effects will be included rather than fixed effects for practices. A similar methodology will be used for the secondary outcomes of comparisons of mortality rates (secondary outcomes 3a and 3b). A subsequent analysis will compare the outcomes of those with EarlyCDT positive in comparison to those in the intervention group with EarlyCDT negative (primary contrast for this analysis) and those in the control group (secondary analysis 1). Comparisons of proportions (secondary analyses 1 and 4) will be carried out using chi square tests. Fishers exact test will be used if the numbers of events are small.

The analyses of the questionnaire responses (secondary analysis 5) will be carried out using the appropriate 2 sample t tests and regression methods at baseline. Non parametric tests will be used if there is evidence of non-normal scores. Multilevel models will be used to analyse the repeated scores during follow up.

Poisson regression models, adjusting for follow up time if necessary, will be used to investigate the other clinical measures (secondary outcomes 6 and 7).

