### **8.7.3 Test results**

False positives and false negatives are explained as follows:

No medical test is completely accurate. This blood test is expected to pick up about 40 in 100 cases of lung cancer and detect the cancer at an early stage. However this means it doesn't pick up all cases of lung cancer. So even if your test is negative, or if you are in the non-test group, it is important that you see your GP if you are unwell in any way that could be due to lung cancer. This includes persistent cough, coughing up blood, shortness of breath, weight loss or loss of appetite.

As no medical test is completely accurate, the blood test will be positive in a small number of people who do not have early lung cancer. This will happen to about 11 out of every 100 people who have a positive test result. These people will be offered chest X-rays and lung scans to see if they have lung cancer. People with a negative blood test will not get any X-rays or scans.

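### Secondary objective 4 (test accuracy) is paired with a late-stage count that cannot measure accuracy, and its all-stage companion is verified differently in test-positives and test-negatives

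*Protocol*

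**What the plan says.** Section 1.4.2 sets objective 4: "to obtain refined estimates of the sensitivity, specificity, positive predictive value and negative predictive value of EarlyCDT-Lung test". The objectives and outcomes table, the Summary's list of secondary outcomes and section 1.5.2 attach two outcomes to it, both at 2 years:

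- (i) "the number of patients with stage 3, 4 or unclassified lung cancer at diagnosis in the EarlyCDT-Lung test-positive group", against the same count in test-negatives;
- (ii) "stage at diagnosis in the EarlyCDT-Lung test-positive and EarlyCDT-Lung test-negative group".

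The Summary's version says the estimates are to be supplied by these two outcomes. Section 7.2 states the analysis: "Comparisons of proportions (secondary analyses 1 and 4) will be carried out using chi square tests", with Fisher's exact test for small numbers.

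Verification depends on the test result. Table 1 in section 2.4 schedules a chest X-ray at baseline and CT at 0, 6, 12, 18 and 24 months for test-positives. For the others, section 8.7.3 says: "People with a negative blood test will not get any X-rays or scans". Controls get no study imaging either, and section 4.1 says they are "advised and counselled identically to those with a negative test result". Everyone is followed through the Scottish Cancer Registry.

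**The concern.** An accuracy estimate needs a definition of disease that does not depend on the test result or on what is done because of it. Neither outcome gives this cleanly.

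Outcome (i) counts events that the imaging of positives is meant to prevent. The better the pathway works, the fewer late-stage cancers remain among positives, and the worse the test looks.

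Outcome (ii) is not restricted by stage, so it escapes that problem. But a cancer in a positive can be found by scheduled CT, while one in a negative is counted only if it comes to clinical diagnosis. The protocol does not acknowledge this difference. Section 7.2 plans contrasts of positives with negatives and of positives with controls, but none of negatives with controls, which is the contrast between two groups without study imaging.

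The protocol says the trial will inform the test's suitability for a large-scale screening service, so accuracy figures from it would carry weight.

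**Working it through.** **Inputs.** Section 7.1: 5,000 per arm; late-stage risk over two years 2.4% v 1.56%, i.e. 120 v 78 events; 85% power, two-sided 5%. Section 1.1: "statistical calculations are based on the 41% sensitivity and 93% specificity of the Early CDT-Lung test"; positivity rate no different in early and late disease; 85% of lung cancers undiagnosed until advanced. The last is used here, as an assumption, to turn late-stage counts into all cancers.

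**The plan's own figure.** For two proportions with mean 0.0198, n = [1.960·√(2·0.0198·0.9802) + 1.036·√(0.024·0.976 + 0.0156·0.9844)]² / 0.0084² = 4,938 per arm; power at 5,000 is 85.4%. The 120 and 78 events are therefore a consistent base.

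**Outcome (i) as the disease definition.** Without the intervention, positives hold 0.41 × 120 = 49.2 late-stage cancers and negatives 0.59 × 120 = 70.8. If all 42 averted cases come from positives, the only group given study imaging, positives keep 49.2 − 42 = 7.2. Apparent sensitivity is 7.2/78 = 9.2%.

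For a reduction r the formula is (0.41 − r)/(1 − r):

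| Reduction r | Apparent sensitivity |
|---|---|
| 0% | 41.0% |
| 20% | 26.3% |
| 35% (planned) | 9.2% |
| 41% | 0% |

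The 9.2% does not depend on the 85% share.

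**Outcome (ii), all stages.** 120/0.85 = 141.2 cancers per arm: 57.9 in positives, 83.3 in negatives. False positives are 0.07 × (5,000 − 141.2) = 340.1, so 398 test positive. With no effect of CT on the number of cancers found, sensitivity is 57.9/141.2 = 41%, PPV 57.9/398 = 14.5% and NPV 98.2%. The late-stage problem has gone.

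Now let CT reveal a fraction x of extra cancers in positives within 24 months (x is an assumption). Sensitivity = 57.9(1+x) / [57.9(1+x) + 83.3]; PPV = 57.9(1+x)/398.

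| x | Sensitivity | PPV | Observed NPV | NPV if negatives were scanned with the same yield |
|---|---|---|---|---|
| 0 | 41.0% | 14.5% | 98.2% | 98.2% |
| 10% | 43.3% | 16.0% | 98.2% | 98.0% |
| 25% | 46.5% | 18.2% | 98.2% | 97.7% |
| 50% | 51.0% | 21.8% | 98.2% | 97.3% |

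Sensitivity is too high against either form of equal verification (neither group scanned, or both scanned with the same proportional yield), since both return 41%. PPV is too high only against verification without study imaging. NPV is too high only if undiagnosed cancers in negatives belong to the target. Specificity moves little (93.0% to 93.6%).

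**Control-arm estimate.** 1 − 83.3/141.2 = 41%. The standard error of the log ratio is √(1/83.3 + 1/141.2) = 0.138. The ratio's interval is 0.59 × exp(±1.96 × 0.138) = 0.450 to 0.773, so sensitivity runs from about 23% to 55%. The within-arm binomial interval is 41% ± 1.96·√(0.41 × 0.59/141.2), i.e. 33% to 49%: narrower, but around a figure open to the upward shift above.

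**The case against.** The strongest reply is that no passage defines sensitivity as late-stage positives over all late-stage cases. A reader might infer that objective 4 rests on the late-stage count alone, that its estimates are biased downward and upward at once, or that a 9% figure would be published. The documents do not support this. Outcome (ii) stands beside (i) without stage restriction and, summed over stages with registry follow-up, gives the all-cancer table. The downward bias arises only if (i) defines disease. The estimator may also be in an analysis plan not shown. All this stands, and limits the point on (i) to an unsuitable outcome paired with the objective. It does not make (i) suitable: the protocol lists it first among the sources of the accuracy estimates, and a chi-square test yields none of the four measures.

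Second, differential verification is built into the intervention, and cancers found by CT are real. That is fair. Scanning negatives would change the design, and some will have clinical imaging anyway: secondary outcome 7 counts such investigations in every group. What remains is unequal scheduled verification that the reported figures should disclose. Its size rests on an assumed x.

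Third, the control arm is not a complete remedy. Negatives and their GPs know the result, and the protocol itself plans to assess harms of a negative result. If reassurance delays presentation, the control-arm estimate is too high. It also gives sensitivity only. These limits stand, so it belongs beside the 2x2 table, not in place of it.

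Nor does section 7.2.1 say that accuracy estimates feed the long-term economic model; that consequence should not be claimed.

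**Conclusion.** The point holds in two conditional parts. Outcome (i) cannot measure accuracy: used as the disease definition, it would show about 9% for a 41% test at the planned effect, given positivity independent of stage and the whole reduction arising in positives. Outcome (ii) avoids this, but the within-arm table is differentially verified and tends to overstate sensitivity. For PPV and NPV the overstatement depends on the target chosen. The direction for sensitivity follows from the design if CT brings diagnoses forward into the 24 months; the amount is not fixed by the document, and 43% to 51% merely corresponds to x of 10% to 50%. The primary outcome is unaffected. The outcome wording should be changed.

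**What to change.** 1. In the objectives and outcomes table, the Summary and section 1.5.2, define objective 4 on lung cancer of any stage diagnosed within 24 months of randomisation. Drop stage 3/4/U as an accuracy measure and keep it as a descriptive comparison of positives with negatives.
2. Report the within-arm 2x2 figures as differentially verified, with cancers detected by study CT and those presenting clinically shown separately.
3. Add to section 7.2 a control-arm estimate of sensitivity: 1 minus the ratio of cancers in test-negatives, per participant randomised to the intervention arm, to cancers per participant in the control arm. State that it gives sensitivity only and assumes that a known negative result does not delay presentation.

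The cost is wording and one added analysis: registry follow-up already covers every participant, and secondary outcome 1 already counts cancers "in the different stages at diagnosis (3/ 4/ U/ other) in the intervention arm and the control arm". No clinical procedure changes. The price is precision, about 23% to 55% around 41% if each arm would have about 141 cancers without study imaging.
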